## Abstract

**Background:**

In-person relationship education classes funded by the federal government tend to experience relatively high attrition rates and have only a limited effect on relationships. In contrast, low-income couples tend to report meaningful gains from web-based relationship education when provided with individualized coach contact. However, little is known about the method and intensity of practitioner contact that a couple requires to complete the web-based program and receive the intended benefit.

**Objective:**

The aim of this study is to use within-group models to create an algorithm to assign future couples to different programs and levels of coach contact, identify the most powerful predictors of treatment adherence and gains in relationship satisfaction *within* 3 different levels of coaching, and examine the most powerful predictors of treatment adherence and gains in relationship satisfaction *among* the 3 levels of coach contact.

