### Participants

A total of 226 couples were randomly assigned to the OurRelationship coach condition, 145 couples were assigned to the OurRelationship contingent coach condition, and 145 couples were assigned to the OurRelationship automated (ie, email only) condition. Similarly, 222 couples were assigned to the ePREP coach condition, 143 couples were assigned to the ePREP contingent coach condition, and 143 couples were assigned to the ePREP automated (ie, email only) condition. A total of 224 couples were assigned to the waitlist control condition. In total, 4 individuals from the OurRelationship coach condition, 2 from the OurRelationship contingent coach condition, and 2 from the OurRelationship automated condition asked to discontinue and have their data removed from the study. Furthermore, 3 individuals from the ePREP coach condition, 2 from the ePREP contingent coach condition, and 3 from the ePREP automated condition asked to discontinue and have their data removed from the study.

In total, 47.5% (1178/2480) of the sample identified as male, and 52.5% (1302/2480) of the sample identified as female. The average length of the relationship was 5.74 years (SD 5.18). Most of the participants reported belonging to an opposite-gender relationship (2318/2480, 93.47%), and a smaller percentage were in same-gender relationships (162/2480, 6.53%). Most participants identified as White non-Hispanic (1520/2480, 61.29%), fewer identified as Black (434/2480, 17.5%), White Hispanic (279/2480, 11.25%), Black Hispanic (28/2480, 1.13%), American Indian or Alaskan Native (23/2480, 0.93%), Asian (17/2480, 0.69%), Hawaiian or Pacific Islander (4/2480, 0.16%), and Biracial (86/2480; 3.47%); and 3.59% (89/2480) of participants belonged to a race that was not listed. Furthermore, 6.81% (169/2480) of participants did not have a degree or diploma, 12.3% (305/2480) had earned a general education diploma, 14.23% (353/2480) had completed high school, 8.23% (204/2480) had a technical or vocational certification, 22.54% (559/2480) had some college degree, 8.83% (219/2480) had graduated with an associate’s degree, 10.69% (265/2480) had a bachelor’s degree, and 2.38% (59/2480) had a master’s or advanced degree.

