#### Data Analysis Plan for Aim 3: Predicting Between-Group Treatment Outcomes

Assuming that the models from the previous aim have levels of prediction accuracy, each of the within-group models will be used to generate predicted outcomes for each couple’s likelihood of adhering to the program as well as their treatment gains, creating counterfactual estimates of program completion and treatment gains as if each couple in the data set completed each intensity and method of coach contact [14].

To do this, the within-group models built in aim 1 will be used to generate potential outcomes for each couple’s likelihood of adhering as well as their gains in a (1) full coaching, (2) automated coaching, and (3) contingent coach conditions. If, in aim 1, the interaction terms result in a better RMSE, models will be constructed based on treatment assignment (ie, OurRelationship or ePREP) and coach assignment (ie, full, contingent, or automated). The estimates between the conditions for each couple’s between-group treatment differences between the full and automated coaching conditions can be understood as:

where 
[figure not shown]
 is the between-group likelihood of treatment adherence or gains for couple x, *Ŷ*(*x, Full Coach*) is the within-group likelihood of treatment adherence or gains for couple x in the full-coach condition, and *Ŷ*(*x, Contingent Coach*) is the within-group likelihood of treatment adherence or gains for couple x in the contingent coach condition [14]. These hypothetical between-group outcomes will then serve as dependent variables in a second random forest to calculate VIMP, which will identify the most powerful predictors of between-group differences. After identifying the most powerful predictors using VIMP, a multiple regression model will be estimated using the reduced set of variables to aid in the interpretation of the main effects. This process will thereby help clinicians determine which couples should be assigned to which level of coach contact.

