## Results

Data collection was completed in October 2020 and data are being prepared to be analyzed. Overall, 63.8% (286/448) of individuals completed the material in the OurRelationship coach condition, 53.8% (155/288) of couples completed the OurRelationship contingent coach condition, and 54.5% (157/288) of individuals completed the OurRelationship automated (ie, email only) condition. Similarly, 69.4% (306/441) of couples completed the content in the ePREP coach condition, 74.2% (210/283) completed the content in the ePREP contingent coach condition, and 66.2% (188/284) of couples completed content in the ePREP automated (ie, email only) condition. Currently, no other outcomes except for completion rates have been analyzed. Given the large sample size within and between conditions, the current sample is large enough to identify potential predictor variables and evaluate their prediction accuracy. This study is expected to conclude in the summer of 2022.

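### Aim 3 ends in advice on which couples get which coaching level, but no step checks the predicted differences, or a rule built on them, against randomised outcomes

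*Protocol article*

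**What the plan says.** The Objective in the Abstract of the protocol article puts first the intention to "create an algorithm to assign future couples", covering both program and coaching level. The Aim 3 section ends by saying that the process will "help clinicians determine which couples should be assigned to which level of coach contact". The Discussion hopes to match couples to the programming that benefits them most.

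The steps in between are set out in order:
- **Aim 1** fits a random forest within each coaching level, or within each of six program-by-level cells if program interactions matter. Performance on test data is judged by sensitivity, specificity and predictive values for completion, and by RMSE for satisfaction.
- **Aim 3** assumes that these models predict adequately, with no threshold. It predicts every couple's outcome under every level and subtracts one prediction from another. The differences become the dependent variable of a second forest, predictors are ranked by VIMP, and a regression is fitted to the reduced set.

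The article defines no rule that turns predictions into an assignment and no quantity that measures what assigning by a rule would achieve. The Results call the sample large enough to find predictors and evaluate prediction accuracy. They do not address precision for the benefit of a rule.

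**The concern.** Accuracy within a level is a different property from knowing which level suits a couple. A forest can predict completion well in each level, for instance through stress or motivation, and carry no information on whether full, contingent or automated coaching is better for that couple. Subtracting two such forests leaves their separate estimation errors, which differ from couple to couple. The second forest, its VIMP ranking and the regression then describe a quantity that may be largely noise.

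At stake is the closing step. Program administrators could be advised to tailor coaching with no evidence that tailoring does better than giving every couple the same level. Coaching was randomised, so the data could speak to this directly.

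**Working it through.** The article gives no power, precision or benefit figure for an assignment rule, so there is none to reproduce. The base figures were checked first and the Aim 3 steps were then simulated.

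**Inputs**
- Full coaching (Participants): "A total of 226 couples were randomly assigned to the OurRelationship coach condition", plus 222 for ePREP, so 226 + 222 = 448 couples.
- Contingent: 145 + 143 = 288. Automated: 145 + 143 = 288.
- All groups: 226 + 145 + 145 + 222 + 143 + 143 + 224 (waitlist) = 1248, which agrees with the stated total.
- Completion (Results), pooled over programs and counted on individuals: full (286 + 306)/(448 + 441) = 66.6%; contingent (155 + 210)/(288 + 283) = 63.9%; automated (157 + 188)/(288 + 284) = 60.3%; all 1302/2032 = 64.1%. The six separate percentages reproduce.
- Predictors: 19, counted from the Measures sections.

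**Direction.** Let Ŷ(x, a) be the prediction for couple x under level a. The mean over couples of maxₐ Ŷ(x, a) can never be below maxₐ of the mean of Ŷ(x, a). It is above as soon as the predicted ranking of levels differs between couples. Read as benefit, the predictions therefore favour tailoring whatever the truth.

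**Size.** One forest per level (448/288/288), every couple predicted under every level, and out-of-bag prediction for the couple's own level. Assumptions: 19 independent normal predictors, 150 trees, 12 replicates per row, programs pooled, no missing data, and three simply randomised levels. None of the scenarios has effect modification (on the logit scale where the levels differ).
- Apparent gain = mean of the highest prediction minus the mean prediction under the best single level.
- True gain = the same comparison using the simulated probabilities.
- Held-out estimate = five-fold, inverse-probability-weighted outcome of couples whose level agreed with the rule, minus the single level that was best in the training folds.

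| Completion scenario | Min. leaf | Apparent gain (points) | True gain | Held-out mean (SD over replicates) |
|---|---|---|---|---|
| No predictor effect, equal levels | 1 | +6.1 | 0 | -1.1 (4.0) |
| | 5 | +5.1 | 0 | +1.1 (3.7) |
| Prognostic predictors, equal levels | 1 | +6.4 | 0 | +0.3 (3.5) |
| | 5 | +5.2 | 0 | +0.5 (2.9) |
| Prognostic predictors, pooled rates 66.6/63.9/60.3% as intercepts | 1 | +6.3 | -2.2 | -0.1 (2.7) |
| | 5 | +4.6 | -2.1 | -1.1 (2.4) |

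The apparent gain was positive in every replicate (minimum +2.7 points). The SD of the predicted full-minus-automated difference was 11.5 to 13.5 points. For a continuous outcome the apparent gain was 0.12 to 0.13 SD with a true gain of zero; the held-out mean was -0.02 to +0.03 SD.

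**Sensitivity to tuning.** In a separate run of the first scenario (8 replicates), raising the minimum leaf from 1 to 60 reduced the apparent gain from 6.8 to 0.9 points.

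**Precision of a held-out estimate.** 1.96 × 2.4 = 4.7 and 1.96 × 4.0 = 7.8, so a 95% CI of roughly ±5 to 8 points.

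**The case against.** Five points can be made for the plan.

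1. **Aim 3 is conditional on prediction accuracy.** With pure-noise predictors, sensitivity plus specificity minus 1 was about zero, so the condition should screen that case out. This stands, and the noise rows should not carry the argument. The prognostic rows do: those models predict outcomes within each level, and a condition without a threshold that looks only within levels does not stop them.
2. **The size depends on forest settings that the article does not fix.** This stands. Only the direction is general.
3. **The mean predicted benefit is not a planned output.** This stands. The figures show what the differences would suggest if read as benefit.
4. **The aims promise prediction and predictors, not proof that tailoring works.** This stands as far as it goes: the section on aims posits no hypothesis for the third aim, and building and evaluating a rule can be separate stages. The closing sentence of Aim 3 still gives assignment guidance as the result.
5. **An article condenses, and the preregistration announced under Procedure is not shown.** That would excuse missing detail. Here the article sets out the whole chain from models to clinical conclusion, and the chain as stated has no check on the differences.

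**Conclusion.** The point holds as a mismatch between conclusion and method. The plan validates prediction within levels and then draws guidance about choosing between levels. With the trial's arm sizes and prognostic predictors that act identically in all levels, the differences would suggest a gain of about 5 to 6 points in completion at minimum leaf 5 and 1. The true gain was zero, or about 2 points negative when levels differed as in the Results. These sizes rest on the assumed forest settings, independent predictors and few replicates; heavier smoothing shrinks them, to about 1 point at minimum leaf 60 in the noise case.

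A reader might infer that the study will report a false benefit of this size, that its stated question is whether tailoring beats one level for all, or that tailoring cannot work here. The document supports none of these. It plans no such benefit figure, its three aims do not pose that comparison, and the simulation assumes absence of effect modification rather than showing it.

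The predictor analyses can go ahead. The assignment advice should not rest on them alone.

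**What to change.** Add the following to the planned preregistration. The Results say that only completion rates have been analysed so far.

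1. Prespecify the rule, for example the level with the highest predicted outcome, separately for completion and satisfaction.
2. Learn it by cross-fitting. In held-out couples, estimate the mean outcome under the rule minus that under full, contingent and automated coaching for all, each with a 95% CI, by inverse-probability weighting. Do this by program as well if Aim 1 keeps six models.
3. Let the weights follow the actual randomisation, and state its probabilities. Procedure describes a second randomisation only for automated-start couples inactive for more than two weeks. If that is what happened, couples never re-randomised are consistent with both the automated and the contingent regime. They count towards both, with weight 1/P(automated start); re-randomised couples get 1/[P(automated start) × P(second allocation)]. The Participants counts (145/145 and 143/143, with all 1248 couples accounted for) suggest instead that every automated-start couple was allocated to one or the other. In that case arm-level weights suffice. The article should say which applies.
4. Word the Aim 3 conclusion as hypothesis-generating unless this estimate supports tailoring.

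The cost is extra analysis on existing data, a CI of roughly ±5 to 8 points for completion (simulation-based, so modest gains would probably remain inconclusive), and possibly a less favourable conclusion.

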**Methods:**

To accomplish these goals, this project intends to use data from a web-based Sequential Multiple Assignment Randomized Trial of the OurRelationship and web-based Prevention and Relationship Enhancement programs, in which the method and type of coach contact were randomly varied across 1248 couples (2496 individuals), with the hope of advancing theory in this area and generating accurate predictions. This study was funded by the US Department of Health and Human Services, Administration for Children and Families (grant number 90PD0309).

**Results:**

Data collection from the Sequential Multiple Assignment Randomized Trial of the OurRelationship and web-based Prevention and Relationship Enhancement Program was completed in October of 2020.

**Conclusions:**

Some of the direct benefits of this study include benefits to social services program administrators, tailoring of more effective relationship education, and effective delivery of evidence- and web-based relationship health interventions.

**International Registered Report Identifier (IRRID):**

DERR1-10.2196/33047

## Introduction

### Background

It is estimated that one-third of marriages in the United States are classified as relationally distressed [1]. Individuals with low-income experience, especially high rates of relationship distress and divorce, report significantly lower marital quality, and experience greater fluctuations in marital quality than high-income earners [2-4]. Low-income couples also have higher levels of alcohol use and infidelity and recent analyses indicate that a meaningful percentage break up during federally funded trials [4-6]. Even when low-income couples have access to free relationship education, they are only able to complete between 10% and 60% of the offered classes in nationwide studies [3,7]. Furthermore, a recent meta-analysis of relationship education for low-income couples revealed that even among the statistically significant findings, the effect sizes were trivial (eg, Cohen *d*=0.06-0.09) [8] and not meeting the widely accepted *small* cutoffs for a meaningful-sized change (ie, Cohen *d*≥0.20) [9]. In the light of these limitations, the authors of this meta-analysis called for innovations in curriculum design, improvements in programmatic elements, and exploration of new ways to sustain participant engagement among low-income couples [8].

### The Law of Attrition and Precision Medicine

Attrition problems are not unique to the field of relationship education and appear to be an inevitable outcome of web-based randomized controlled trials (RCTs) [10]. This has led some to propose the law of attrition [11], which argues that participant dropout is a fundamental methodological challenge inherent in RCTs, which makes investigating the effects of web-based interventions particularly challenging. The law of attrition argues that couples are initially drawn to web-based programs because of their innovative properties (eg, they are brief, can be completed from home, and are inexpensive). However, after registering for the program, reasons that individuals may not continue their participation could include (1) being exposed to conflicting messages about the program, (2) rejecting the program for something better, or (3) leaving the program as the individual was dissatisfied with the services they received [11].

Others have argued that the law of attrition could be enhanced by the inclusion of user characteristics [10]. User characteristics (ie, couple- or individual-level differences) may moderate adherence to the intervention. Some of these differences may include relationship problems, levels of motivation to complete the program, baseline levels of symptomology, the need for anonymity, lack of available resources, or living in a remote location. Simply because of couple-level differences, some percentage of the population is likely to complete and benefit from web-based interventions, and some percentage of the population will not, with most of the population likely falling somewhere in between [12].

Thus, determining who is likely to drop out of the program and who is likely to complete the program at the program outset would be a major benefit to administering effective web-based relationship education. Focusing on completion of the program (and its specific activities) rather than aiming to increase the desired outcome (eg, relationship satisfaction) not only decreases attrition but may also increase the desired behavioral changes [12]. The addition of couple-level differences to the law of attrition suggests that sensitivity to couple-level differences would likely decrease attrition and increase the efficacy of web-based interventions.

Recently, strides have been made in machine learning to mirror these ideas, allowing researchers to predict and compare the predicted treatment effects for couples [13,14]. This approach is often referred to as precision medicine. At the heart of this area of research is the idea that average treatment effects from an RCT may not generalize well to treatment targets (ie, individuals or couples). Although treatment decisions made by humans are typically based on a small number of characteristics (eg, race, ethnicity, or gender), humans are unable to make decisions at the multivariate level without computational resources. The ability to estimate couple-level treatment effects would allow for treatment options that are directly tailored to estimate the unique needs of each unique couple that a practitioner would encounter [13,14].

### A Review of Evidence-Based Relationship Education Programs

This precision medicine and machine learning approach is relatively new to the field of relationship education and web-based health interventions. Thus, starting a precision medicine approach with programs that have already been shown to be evidence-based and beneficial would be worthwhile. Arguably, OurRelationship and web-based Prevention and Relationship Enhancement Program (ePREP) are the 2 web-based relationship education programs with the largest evidence base. OurRelationship and ePREP contain only 6 to 10 hours of content—substantially less content than comprehensive programs previously delivered by the federal government. The OurRelationship program is a web-based, self-help adaptation of integrative behavioral couple therapy that emphasizes acceptance and change [15]. The program includes tailored feedback, filmed examples of couples experiencing relationship distress, and i and activities encouraging couples to be more mindful of their relationship dynamics. Currently, the standard of care includes delivering the program in conjunction with four 15-minute calls with a coach to reinforce the material that is learned throughout the program [15-17]. In a nationwide RCT of 300 couples, this short program led to small- to medium-sized gains (Cohen *d*=0.15-0.69) in key areas of individual and relationship well-being compared with a waitlist control group [16]. Furthermore, couples maintained these effects for at least a year following the intervention [18]. The OurRelationship program appears to benefit couples regardless of income, demographic characteristics, and sexual orientation across a number of outcomes of interest (eg, depression, anxiety, relationship satisfaction, relationship positives, and relationship negatives) [19].

The ePREP program is a web-based adaptation of the Prevention and Relationship Enhancement Program, which emphasizes skill building [20,21]. Accordingly, ePREP introduces a set of healthy communication strategies to reduce conflict in relationships. Some of these strategies include the time-out strategy and the speaker-listener technique, as well as how to maintain fun and friendship in the relationship after the program has ended. In several randomized clinical trials, those that have participated in ePREP have reported small- to medium-sized gains in relationship functioning [21-24]. Follow-up studies have found that the improvements in functioning attributable to ePREP were maintained over a 10- to 12-month follow-up period [22,24]. In addition, those who master the strategies taught in ePREP experience superior improvements in constructive communication and relationship satisfaction [23].

Recently, both OurRelationship and ePREP were compared with one another and to a waitlist control condition in a large Administration for Children and Families (ACF)–funded RCT with low-income couples (N=742) [17]. When delivered in conjunction with four 15-minute coach videoconferences or telephone calls, adherence rates in the OurRelationship and ePREP programs were equal, with 69% of couples completing the assigned material. When compared with the waitlist control condition, those in the OurRelationship and ePREP conditions reported increases in relationship satisfaction (Cohen *d*_OurRelationship_=0.53; Cohen *d*_ePREP_=0.42) and emotional support (Cohen *d*_OurRelationship_=0.46; Cohen *d*_ePREP_=0.36), along with decreases in breakup potential (Cohen *d*_OurRelationship_=−0.53; Cohen *d*_ePREP_=−0.43), communication conflict (Cohen *d*_OurRelationship_=−0.78; Cohen *d*_ePREP_=−0.54), and intimate partner violence (IPV; Cohen *d*_OurRelationship_=−0.10; Cohen *d*_ePREP_=−0.08) [17]. Furthermore, these effects were maintained over a 6-month follow-up period [17]. When the 2 programs were compared, only one significant effect emerged; those in the OurRelationship program experienced greater decreases in communication conflict when compared with those in the ePREP program (Cohen *d*=−0.24) [17]. These findings were later reproduced in an independently collected sample [25].

